#### Data management

The focus groups and patient interviews will be audio recorded and field-notes will be written to record any instances of non-verbal communication or reaction to any of the discussions. Digital recordings will be transcribed in full and verbatim. Transcripts will be anonymized and subsequently uploaded to QSR NVivo 10 (QSR International) qualitative software for data management and coding.

### Framework analysis

Data will be analyzed to identify problems with systems and procedures that need addressing as well as patient attitudes and experiences. The most appropriate analytic method to achieve this for both the focus group and interview data is framework analysis, an adaptable approach originally developed for use in applied policy research with clear objectives [38]. It is a methodical approach that follows a clear and documented process, but as with other qualitative approaches it relies on the researcher to determine the quality of the analysis [38]. Framework analysis will be carried out in line with Ritchie and Spencer’s five interconnected steps described in Table 4[38].

**Table 4 T4:** **Framework analysis - Ritchie and Spencer’s five interconnected steps**[38]

**Familiarization:**	The researcher will immerse themselves in the data by re-listening to interview recordings and re-reading transcripts and field notes. The researcher will document central ideas and recurring themes.
**Identifying a thematic framework:**	An index of themes will be created, informed by the original research aims around understanding recruitment and retention, but also by issues raised by the participants in the data.
**Indexing the data:**	The index will be applied to each transcript by coding them with the themes from the thematic framework. During this process, the framework may be adjusted, adding new themes and subthemes as they emerge. The adjusted framework will then be applied to subsequent transcripts and reapplied to existing transcripts to ensure all data is appropriately coded.
**Charting:**	A matrix will be created of themes and participants. Data will be lifted from the transcripts and arranged according to thematic references. The data is summarized by the researcher, rather than verbatim quotes included, and referenced back to the original data.
**Mapping and interpretation:**	Charts and research notes will be reviewed to compare and contrast the perceptions and experiences of participants.

The qualitative components of the study (focus groups with clinicians and qualitative interviews with patients and relatives and/or carers) will provide rich data in relation to the attitudes of clinicians recruiting to the study and to patients and their relatives’ motivations to participate in the trial, perceived benefits and burdens, and reasons for withdrawal from the trial. The findings of the qualitative study will be used by the Trial Management Group to assess potential alterations to trial design, and will be used to complement the reporting of the full trial, where appropriate.

### UK wide survey exercise

This component of the study will comprise telephone and web-based surveys to develop a classification and enumeration system for current CAT models and pathways of care. The pilot will be used to identify the relevant variables in the CAT journey and shall be used to develop the most important questions to be asked in the web-based survey. The survey shall then be distributed as widely as possible in order to gain a maximum breadth of understanding pertaining to the patient journey and different service models. Responsibility for the management of patients with ongoing malignancy post-VTE varies across different regions; in some, anticoagulation is managed entirely through the hematology service, whilst some oncology centers will take responsibility for CAT management. Other models are known to exist in which a shared care agreement supports CAT management predominantly in the primary care setting. The survey will be structured around the patient pathway from identification of a VTE, early management and late management developed from the focus groups. We will then undertake a UK wide survey exercise with relevant stakeholders from primary and secondary care. This will initially be in the form of a telephone survey to essentially pilot and clarify the survey tool. The survey will explore the views and experiences of relevant clinical stakeholders involved in the CAT journey from diagnosis to ongoing management, and will include clinicians and allied health professionals from radiology, hematology, oncology primary care and pharmacy. Initial questions shall be designed around the findings from the focus group data in order to conduct semi-structured interviews. These findings shall then inform the design of a more extensive web survey sent out to doctors, nurses and allied health professionals potentially involved in the care of patients with CAT, and will allow for classification and enumeration of the models of care. This will also be triangulated with available documentary evidence on pathways of care. A particular focus will be on the management of transition points between settings and how continuities in care are assured. Respondents will be encouraged to submit any local documents they use on care pathways.

### Outcome measures

The primary outcome measures are: the number of eligible patients identified over 12 months, the number of recruited patients (randomized participants) over 12 months (target recruitment rate of 30% of eligible patients), and the proportion of participants with recurrent VTEs during trial follow up. VTE will be objectively confirmed through radiological investigation. DVT will be confirmed through Doppler ultrasonography or venography. PE shall be confirmed through a computerized tomography (CT) pulmonary angiogram. The secondary outcome measures are: completion of trial protocol, quality of life, symptom assessment, patients’ and relatives’ experiences of taking part in the trial, and the attitudes of clinicians towards the ALICAT trial.

Completion of trial protocol will be assessed six months after randomization to ascertain the attrition rate due to patient choice or death during the study period. Participants choosing to withdraw from either arm of the study protocol will be invited to participate in a qualitative interview to explore their reasons for withdrawal.

Quality of life will be measured using the EORTC QLQ-C30 Version 3.0 and EQ-5D-5 L at three monthly intervals for six months. The EORTC QLQ-C30 [39], Version 3.0, has become a benchmark measure of quality of life in patients with cancer. It contains five functional scales (physical, role, cognitive, emotional and social), three symptom scales (pain, nausea and/or vomiting, and fatigue), global health and quality of life scales, and several other single items. The EQ-5D-5 L [40] is a short quality of life tool, designed to complement other measures and is recommended by the National Institute for Health and Care Excellence for use in economic analyses [41]. The ALICAT study will identify key cost drivers to inform the design of a future definitive phase three trial, which will include a cost utility study. Orders of magnitude of differences in costs and outcomes identified in the EQ-5D-5 L will help in the estimation of anticipated effect sizes for the full trial.

Symptom assessment will be measured using the Edmonton Symptom Assessment System Revised (ESAS-r) at three monthly intervals for six months. The ESAS-r is used to capture patients’ perspective on their symptoms, providing an indication of severity of nine symptoms: pain, tiredness, drowsiness, nausea, lack of appetite, depression, anxiety, shortness of breath, and wellbeing [42,43]. In addition, we will look for symptoms which are likely to be specifically due to VTE (new or worse leg swelling and/or pain, new or worse breathlessness, pleuritic chest pain).

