**Dose for renal impairment:**	Follow the SPC. Patients with renal impairment should have dose adjustment depending on creatinine clearance/anti factor Xa levels according to local policy.

LMWH, Low molecular weight heparin; SPC, summary of product characteristics; VTE, venous thromboembolism.

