#### RCT sample size calculation

We anticipate there being at least 200 eligible patients per year in total from all three recruitment settings. We assume that not all patients who have been injecting LMWH for five months will agree to continue for a further six months. We are not sure what proportion of patients will be willing to be randomized, but we consider that at least 30% will need to agree in order to make a phase three RCT worthwhile. Therefore, the ALICAT study will aim to assess the feasibility of randomization by determining if at least 30% of potential patients will agree to randomization. We will then calculate the precision of this proportion with a 95% confidence interval. We will also estimate the proportion of patients who experience recurrent VTEs during follow up, which will inform the design of the phase three RCT.

If less than 15% of eligible patients agree to take part in the trial, a phase two RCT may not be suitable as we may not be able to recruit suitable numbers, given that a larger phase three RCT could have more stringent eligibility criteria as a result of this feasibility study. If at least 30% agree to take part, then we would consider that randomizing patients to a larger phase three trial would be feasible. Using a Fleming’s single stage design, setting p1 to 0.15 and p2 to 0.3, and with 5% significance and 90% power, then we will need to approach 62 eligible participants with details of the trial. This design requires that at least 15 out of 62 participants consent to the trial. We therefore propose a two-stage sample size. If at least 15 out of the first 62 participants recruited to the trial accept randomization, then we will continue recruitment into stage two. If fewer than 15 patients agree, we will determine at this stage that randomization within this population is not feasible.

If we expect that 200 will be the maximum potential number of eligible patients, then we can expect to be able to produce a 95% confidence interval for the percentage willing to be randomized of width 13.7% or less. For example, if the percentage is 50%, then we could expect the 95% confidence interval to be 43.15 to 56.85%. If the percentage is 30% we can expect a slightly smaller confidence interval of 23.7 to 36.3%. If only 150 patients are deemed eligible, then we can expect to calculate a 95% confidence interval for 50% randomized of 42.1 to 57.9%.

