#### RCT data collection

Participants randomized to the RCT will be seen at the recruiting hospital clinical or GP practice (as appropriate) approximately 12 and 26 weeks after starting a further six months treatment with LMWH (treatment arm) or after stopping treatment with LMWH after six months treatment off-trial (control arm). Assessments will include VTE treatment and compliance, physical assessment, full blood count, urea, electrolytes, liver function test, bone profile, toxicities, concomitant medications, use of NHS resources (hospital admissions, GP visits, nurse visits: details to be taken from patient diary booklet and patient notes), and quality of life questionnaires (EORTC QLQ-C30, E5D-5 L and ESAS-r). VTE, bleeding events, and serious adverse events will be collected in real time. Adverse events, in particular the secondary outcomes of recurrent VTE or hemorrhagic events, will be monitored by the Independent Data Monitoring Committee. In the event of excessive bleeding or thrombotic events, this committee will advise on early closure of the trial if necessary. Research staff at recruiting sites will be expected to complete trial case report forms (CRFs) that record evidence of primary and secondary outcome measures. Patients will also be asked for optional consent to have their NHS number collected and to be registered with NHS Information Centre Flagging so that the date and cause of death can be collected without longer term follow up.

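### PE counts only if shown on a CT pulmonary angiogram, so the primary recurrence proportion can omit PE proven by other means and fatal PE never imaged

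*Protocol article*

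**What the plan says.** Under Outcome measures, the third primary outcome is "the proportion of participants with recurrent VTEs during trial follow up". Three sentences then define what counts:

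- General rule: "VTE will be objectively confirmed through radiological investigation".
- DVT: "DVT will be confirmed through Doppler ultrasonography or venography".
- PE: "PE shall be confirmed through a computerized tomography (CT) pulmonary angiogram".

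The RCT sample size calculation section says the trial will estimate "the proportion of patients who experience recurrent VTEs during follow up, which will inform the design of the phase three RCT".

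Deaths are handled apart from VTE. The Statistical analysis section reports the percentage who died within six months in each arm. The RCT data collection section asks for optional consent to national flagging "so that the date and cause of death can be collected without longer term follow up". No stated VTE outcome uses the recorded cause.

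**The concern.** The article names two tests for DVT and one for PE, so alternatives were listed where they were wanted. Read literally, the PE sentence shuts out three kinds of event:

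- a PE shown on another contrast CT, such as a cancer staging scan, or on a ventilation-perfusion scan;
- a PE found at autopsy, which also fails the general requirement for radiology;
- a fatal PE in a patient who was never imaged, which appears only among the deaths.

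Every participant has locally advanced or metastatic cancer, and the article itself expects attrition from death, so these situations are foreseeable. At stake is the recurrence risk that phase three is to be designed on. The article also makes the practicality of measuring the primary outcomes a feasibility objective. With one accepted test and no stated record of how events were detected, the trial cannot tell phase three how many events its own definition loses.

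**Working it through.** **1. The plan's own precision figures.** Input: 30 patients per arm (RCT sample size calculation).

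- At 50% the article gives about 33% to 67%. The Wilson interval is 0.5 ± [1.96/(1 + 3.84/30)] × √(0.25/30 + 3.84/(4 × 30²)) = 0.5 ± 0.168, or 33.15% to 66.85%. This matches.
- At 8% the article gives 0 to 19%. The continuity-corrected Wald upper limit is 0.08 + 1.96 × √(0.08 × 0.92/30) + 1/60 = 0.08 + 0.097 + 0.017 = 0.194, with the lower limit cut at 0. This matches.

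Both examples reproduce, though by different interval methods. They are the yardstick for the size of any undercount.

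**2. Undercount.** Let m be the share of true recurrences that the rule does not count. Then recorded risk = true risk × (1 − m), and events lost per arm = 30 × true risk × m. The documents give no value for m. The range 10% to 40% is an assumption for illustration.

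| True risk | m | Recorded risk | Events lost per 30 |
|---|---|---|---|
| 8% | 10% | 7.2% | 0.24 |
| 8% | 40% | 4.8% | 0.96 |
| 20% | 10% | 18% | 0.6 |
| 20% | 40% | 12% | 2.4 |

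At 8% the loss is 0.8 to 3.2 percentage points, against a stated interval 19 points wide. The interval narrows with more patients; the loss does not.

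**3. Direction between arms.** Take assumed true risks of 20% (stop) and 8% (continue), a ratio of 2.5. The sample sizes use the usual two-proportion formula with pooled variance under the null, and assume two-sided 5% and 90% power.

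| m, stop | m, continue | Recorded risks | Points lost, stop / continue | Ratio | n per arm |
|---|---|---|---|---|---|
| 0 | 0 | 20% v 8% | 0 / 0 | 2.50 | 174 |
| 20% | 20% | 16% v 6.4% | 4.0 / 1.6 | 2.50 | 225 |
| 30% | 10% | 14% v 7.2% | 6.0 / 0.8 | 1.94 | 429 |
| 10% | 30% | 18% v 5.6% | 2.0 / 2.4 | 3.21 | 141 |

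With an equal share missed, the ratio is unchanged and only the absolute loss is larger in the higher-risk arm. With unequal shares, the result moves either way. Nothing in the article says which row applies.

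**The case against.** **Objective confirmation is a sound choice in an open-label trial.** Requiring imaging limits how far knowledge of allocation can shape what is called a PE. This stands, and it is why confirmed VTE should remain the primary proportion. It argues for objective evidence, not for one particular scan.

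**The article is condensed.** Rules for fatal, incidental or post-mortem events may sit in the full protocol. That is fair for rules the article omits. Here the article states a rule. If the full protocol is wider, the published sentence misstates it and should be aligned. It is also true that a staging CT satisfies the general radiology sentence while failing the PE sentence, so the two need reconciling in any case.

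**Fatal events are not lost to the trial.** Deaths are reported by arm, serious adverse events are collected in real time, and the data monitoring committee watches thrombotic events. This stands for safety oversight. It does not put those events into the recurrence proportion.

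**Stronger readings a reader might infer.**

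- *That the undercount falls mainly on the arm that stops.* The documents do not say so. It requires a higher true risk in that arm, and even then, with equal shares missed, the relative loss is the same. Clinicians who know the allocation might image patients off LMWH more readily, which would move the undercount towards the continuing arm.
- *That uncounted fatal PE can be sized from the extended-dalteparin cohort in the Background.* The 4.1% recurrence gives 30 × 0.041 = 1.2 events per arm, and 1 − 109/185 = 41% gives about 12 non-completers in 30. Going further needs the share of non-completers who died and the share of those deaths due to PE, and the document gives neither. The cohort was on LMWH throughout, non-completion need not mean death, and the article does not say whether the 4.1% already includes fatal PE.
- *That the trial foresees patients who cannot have contrast.* The nearest text is Table 3: "Patients with renal impairment should have dose adjustment depending on creatinine clearance/anti factor Xa levels according to local policy". That concerns dosing and says nothing about imaging.

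**Conclusion.** The point holds in limited form. As written, the rule excludes PE proven by other objective means and fatal PE never imaged from a primary outcome that is to inform phase three. If such events occur, the recorded recurrence risk is too low. The documents do not give the size. On the assumed 10% to 40% missed, the loss is 0.24 to 0.96 events per 30 at a true risk of 8%, which is minor for a feasibility trial with 30 per arm. It still deserves correction because it is systematic and the estimate is meant to be reused. In the equal-share illustration, recorded rates lead to 225 per arm where true rates need 174. If phase three kept the narrow rule, those extra 51 patients per arm would be the price of uncounted events; if it widened the rule, it would be oversized. No claim about which arm is affected more can be made.

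**What to change.** In Outcome measures:

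- Let PE be confirmed by CT pulmonary angiogram, other contrast CT, ventilation-perfusion scan or autopsy, and extend the general radiology sentence to admit autopsy.
- Record for each event the mode of detection and whether it was incidental or symptomatic, and tabulate both by arm. This also shows whether detection differed between arms.
- Keep objectively confirmed recurrent VTE as the primary proportion.
- Add one supplementary row per arm: confirmed VTE, or death with PE as the recorded cause, using the cause-of-death data described under RCT data collection. State for how many deaths a cause was available.
- Pass both proportions to the phase three design.

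The cost is a change of wording, a small addition to the case report form and one table row. No patient needs an extra scan. The downside is that recorded cause of death is less certain than imaging, rests on optional consent, and may be influenced by knowledge of allocation. The added row should therefore stay supplementary.

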#### Participant recruitment

In order to assess the feasibility of recruiting sufficient numbers of patients to inform a full phase three RCT, the ALICAT study will evaluate recruitment of patients from three different care settings within the UK: oncology outpatients, hematology outpatients, and primary care. Index VTE events shall be identified through primary and secondary care clinical databases and clinical records. In the oncology and hematology outpatient settings, potential participants will already be attending outpatient clinics for management of their cancer or CAT, and potential participants will be screened by a researcher and notified to the site principal investigator. Within the primary care setting, electronic patient records will be used to identify patients receiving treatment doses of LMWH. These records will be screened for patient eligibility of registration, by a researcher based in a primary care research institution. Patients who meet the eligibility criteria will be invited to the participating practice in order to consider participating in the study. The search will be repeated monthly in order to identify incident cases.

Potential patients will be identified when they are approaching completion of their first five months treatment with LMWH for CAT. Suitable patients will be anonymously registered. After written informed consent has been obtained, a screening baseline assessment will be conducted to ensure all the inclusion and exclusion criteria are met (see Table 1). Patients who meet the eligibility criteria will be randomized by the coordinating trials unit to either the treatment arm (continue LMWH treatment for a further six months) or the control arm (discontinue LMWH), using block randomization with varying block sizes and a 1:1 allocation ratio. Randomized patients will be asked to complete three baseline quality of life questionnaires (EORTC QLQ-C30, E5D-5 L and ESAS-r), and to keep a diary card during the six month follow up period, irrespective of the trial arm assigned.

**Table 1 T1:** Inclusion/exclusion criteria and initial assessment for the ALICAT trial

**Inclusion criteria**	1. Receiving LMWH for treatment of CAT for approximately five months
	2. Locally advanced or metastatic cancer
	3. Able to self-administer LMWH, or have LMWH administered by a carer (routine administration by a district nurse is not permissible)
	4. Able to give informed consent
	5. Age ≥16 years.

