**Exclusion criteria**	1. Receiving drug other than LMWH for CAT
	2. Contraindication to continuing anticoagulation:
	a. Known allergies to LMWHs, heparin, sulfites or benzyl alcohol,
	b. Active major bleeding,
	c. History of heparin-induced thrombocytopenia,
	d. Known poor compliance with LMWH,
	3. Confirmed recurrent VTE whilst receiving anticoagulation
	4. Fitted with a prosthetic heart valve.
**Initial assessment**	1. Full blood count, urea, electrolytes, liver function, bone profile
	2. Physical examination
	3. Primary tumor and tumor treatment history
	4. Details of LMWH treatment off-trial
	5. Baseline concomitant medications
	6. Baseline comorbidities (including index VTE and bleeding event history)
	7. Use of NHS resources three months prior to commencing trial treatment.

CAT, Cancer associated thrombosis; LMWH, Low molecular weight heparin; NHS, National Health Service; VTE, Venous thromboembolism.

Information on all potentially eligible patients will be recorded, including whether or not patients were actually eligible for the trial, if they were approached about the trial, if they agreed to randomization, or were approached about taking part in a qualitative interview. Where possible, information on why the patient was not approached, randomized or approached for the qualitative interview will also be recorded.

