Our target registration number for this feasibility trial is therefore 200 patients, of which we hope that at least 60 patients will be randomized into the two groups. Thirty patients per arm will provide enough power to create a 95% confidence interval around the risk of VTE recurrence, which would have a width of 34% or less. As an example, if we found that the risk of VTE occurrence was 50% in the arm that stopped, we would be able to estimate a confidence interval of approximately 33% to 67% or smaller. If the risk of VTE were 8%, the confidence interval would be 0 to 19%.

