#### Statistical analysis

All analyses will be performed on a full intention-to-treat basis, (all patients randomized will be included) and all patients will be analyzed according to their allocated group, whichever treatment they received. We will calculate the percentage of registered patients who were randomized, with 95% confidence interval. We will also calculate the percentage of patients experiencing recurrent VTE recurrence and bleeding events in both groups with 95% confidence intervals. The percentage of patients who died within six months of randomization will be calculated in both arms, along with the percentage of patients who successfully completed six months of trial treatment in the LMWH group. The median QLQ-C30 raw and linear transformed functional scales will be calculated and presented for both arms of the study. No formal subgroup analyses are planned. However, if any treatment effect is found we will investigate whether it is consistent across participant subgroups (defined by all pre-treatment factors collected) although this analysis will be exploratory in nature. Exploratory analyses may be conducted to aid hypothesis generation if a phase three RCT is subsequently developed.

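### The only stated quality-of-life analysis is a per-arm QLQ-C30 median with no difference, interval or baseline adjustment, although baseline scores are collected and between-arm differences are meant to inform phase three

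*Protocol article*

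**What the plan says.** Four places in the protocol article bear on this.

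- **Statistical analysis.** The quality-of-life analysis is one sentence: "The median QLQ-C30 raw and linear transformed functional scales will be calculated and presented for both arms of the study". The same section attaches 95% confidence intervals to the percentage randomized and to the percentages with recurrent VTE and with bleeding, but none to quality of life. It gives no analysis for EQ-5D-5L, ESAS-r or costs.
- **Outcome measures.** Differences are given a purpose beyond description, namely planning phase three: "Orders of magnitude of differences in costs and outcomes identified in the EQ-5D-5 L will help in the estimation of anticipated effect sizes".
- **Participant recruitment.** Baseline scores are collected: "Randomized patients will be asked to complete three baseline quality of life questionnaires (EORTC QLQ-C30, E5D-5 L and ESAS-r"). Under initial assessment, Table 1 lists "Use of NHS resources three months prior to commencing trial treatment". Allocation is made "using block randomization with varying block sizes and a 1:1 allocation ratio", with no stratification factor named.
- **RCT sample size calculation.** The hope is for at least 60 randomized patients, 30 in each arm.

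Under RCT data collection, the same three questionnaires are repeated at about 12 and 26 weeks. The section headed Randomized controlled trial describes the design as open-label.

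**The concern.** The stated analysis and the stated use do not fit well together. Two separate medians describe each arm. They give no estimate of a difference, show no uncertainty, and supply no residual SD for planning. Phase three, however, is to draw on differences.

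A patient's quality of life at entry usually predicts the later score, and earlier resource use usually predicts later cost. With about 30 patients per arm and no stratification named, the arms can differ noticeably at baseline by chance. A follow-up comparison that ignores baseline carries that chance difference as extra noise. Since the values are already collected, leaving them out gives away precision that would cost almost nothing to keep.

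There is also a point of timing. The article has patients who are already randomized fill in the baseline questionnaires. In an open-label trial, knowing that one will stop or continue injections could colour the answers. A baseline score is a sound covariate only if allocation cannot have influenced it.

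**Working it through.** **The plan's own figure at 30 per arm.** The article states no SD, effect size or precision for quality of life or costs. Its only figure resting on 30 per arm is the interval for VTE recurrence at 50%, approximately 33% to 67%. The Wilson interval has half-width [z/(1 + z²/n)] × √(p(1−p)/n + z²/(4n²)). With p = 0.5, n = 30 and z = 1.96 this is (1.96/1.128) × √(0.00833 + 0.00107) = 0.168. The interval is 33.2% to 66.8%, which reproduces the stated figure.

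**Inputs for the quality-of-life check.**
- n = 30 per arm (RCT sample size calculation), all assessed. Full assessment is an assumption.
- Baseline-to-follow-up correlation r = 0.3, 0.5 or 0.7. This is an assumption; the article gives none.
- Results are in SD units, so no SD need be assumed at this stage.
- The comparison is of mean differences, unadjusted against adjusted, because the article defines no difference between medians.

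**Unadjusted.** SE = √(2/30) = 0.258 SD. The 95% half-width is 1.96 × 0.258 = 0.51 SD.

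**Adjusted for baseline (ANCOVA).** SE = √(2/30) × √(1 − r²). The last column is the increase in sample size that would buy the same precision, 1/(1 − r²) − 1.

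| r | √(1 − r²) | SE (SD) | 95% half-width (SD) | Equivalent extra patients |
|---|---|---|---|---|
| 0.3 | 0.954 | 0.246 | 0.48 | 10% |
| 0.5 | 0.866 | 0.224 | 0.44 | 33% |
| 0.7 | 0.714 | 0.184 | 0.36 | 96% |

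**On the EQ-5D-5L scale.** Assume an SD of 0.25, with a range of 0.20 to 0.30. The unadjusted half-width is 0.506 × 0.25 = 0.127 (0.101 to 0.152). Adjusted, it is 0.438 × 0.25 = 0.110 (0.088 to 0.131) at r = 0.5 and 0.361 × 0.25 = 0.090 (0.072 to 0.108) at r = 0.7.

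**Chance baseline difference.** Its standard deviation is also 0.258 SD. The probability that it exceeds 0.25 SD in either direction is 2 × [1 − Φ(0.25/0.258)] = 33%. This is another view of the sampling error above, not an additional harm.

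**With fewer assessed.** If only 20 per arm give follow-up data (an assumption), the unadjusted half-width is 1.96 × √(2/20) = 0.62 SD. Adjusted at r = 0.5 it is 0.62 × 0.866 = 0.54 SD.

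No size is given for costs, because the article offers no SD or correlation for them.

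**The case against.** The strongest objection is that much of this rests on silence. The article condenses a fuller protocol, the analysis plan is not shown, and adjustment of secondary and economic outcomes is commonly left to those documents.

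That stands for EQ-5D-5L and costs. A reader might infer that these differences will come from plain per-arm summaries. The article does not say so: the median sentence covers only the QLQ-C30 functional scales, and EQ-5D-5L and cost differences could be raw, changes from baseline or adjusted. The point is therefore anchored on the QLQ-C30 sentence, which does fix a method.

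Three other strong readings also fail.

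- *Chance imbalance would be mistaken for a treatment effect.* Under randomization the unadjusted difference is unbiased, and chance imbalance is already part of its standard error. The loss is precision.
- *Phase three would be left without the baseline-to-follow-up correlation.* The same instruments are used at baseline and follow-up, so it can be computed from the collected data at any time. The request is only to report it.
- *The baseline data have no planned use.* The Statistical analysis section allows exploratory subgroup work by pre-treatment factors if a treatment effect is found, and exploratory analyses to generate hypotheses for phase three. Neither is said to be baseline-adjusted, but neither rules it out.

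It is also fair to say that the article claims only orders of magnitude that will help, and that a half-width of 0.44 instead of 0.51 SD rarely changes such a reading. That limits the weight of the point. It does not remove the case for a better estimate from data already in hand.

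**Conclusion.** The concern holds in a narrow form and is a minor improvement, not an error that threatens the trial. The single stated quality-of-life analysis gives no difference, no interval and no use of baseline, while between-arm differences in EQ-5D-5L and costs are intended to help set phase three effect sizes by a method the article leaves unstated.

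Baseline adjustment would shorten the 95% half-width by about 5%, 13% or 29% at r = 0.3, 0.5 or 0.7. This assumes 30 assessed patients per arm, a linear relation with baseline and the normal approximation. At the low end of that range the gain is slight. Even at r = 0.7 the half-width remains 0.36 SD, so adjustment does not turn a study of this size into a precise source of effect sizes.

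The timing of the baseline questionnaires has direct support in the wording, since it is "Randomized patients will be asked to complete three baseline quality of life questionnaires" in an open-label design. The article does not establish that patients know their allocation when they answer. It leaves that possible, and the order should be fixed if the scores are to serve as covariates.

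**What to change.** 1. **Statistical analysis.** Keep the medians. Add the 12- and 26-week mean differences between arms, each adjusted for the same score at baseline (ANCOVA), with 95% intervals. Report the residual SD and the baseline-to-follow-up correlation.
2. **Outcome measures.** State that any EQ-5D-5L or cost difference carried to phase three is estimated in the same way, with costs adjusted for resource use in the prior three months. If the full protocol or analysis plan already says this, a cross-reference is enough.
3. **Participant recruitment.** Have the baseline questionnaires completed after consent and before allocation is disclosed.

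Items 1 and 2 change analysis wording only and need no new variables. Item 3 changes the order of assessments: a few patients will complete questionnaires and then not be randomized.
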